### Outcomes {12}

Primary outcomes will encompass the following: (1) the concordance between HR and step count measurements assessed by the biosensor under test compared to standard devices (Polar H10 and ActiGraph, respectively); (2) participant perception regarding the utility of the gamified application for exercise engagement; (3) comparison with the prevalence of adherence to the physical activity protocol between the control and intervention groups; (4) evaluation of exercise capacity through ISWT, including stage and the corresponding phase at which the test was halted; and (5) measurement of oxygen consumption (VO_2_).

Secondary outcomes will include the following: (1) tissue oxygenation assessed via near-infrared spectroscopy (NIRS), (2) subjective perception of exertion during ISWT, (3) evaluation of endothelial function, and (4) assessment of autonomic function.

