### Sample size {14}

Since phases 1 and 2 consist of a pilot study for the clinical evaluation of a biosensor prototype and the gamified application that considers a biofeedback system for performing physical exercises, a convenience sample of 15 individuals without medical contraindications for PA will be studied. Assuming a sample loss of 30%, we will recruit 20 participants.

The third phase will be a noninferiority, investigator-blinded randomized clinical trial of the individuals eligible for the study—considering the same eligibility criteria as in phases 1 and 2, in addition to being sedentary—will be divided into two groups: the intervention group (IG), which will receive the exercise protocol through the biosensor and gamified application, and the control group (CG), which will only receive guidelines for performing PA. Considering a confidence level of 95%, power of 80%, ratio of 1:1 between the CG and IG, and estimated prevalence of adherence to the protocol of 70% and 50% for the IG and CG, respectively, it would be necessary to allocate 104 individuals in each group. Adding 30% for possible follow-up losses, 149 sedentary individuals will be assigned to each group, totalling 298 subjects in the study.

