## Statistical methods

### Statistical methods for primary and secondary outcomes {20a}

Data distribution will be assessed using the Kolmogorov–Smirnov test. Parametric data will be presented as mean ± standard deviation, while non-parametric data will be displayed as median (interquartile range). In phase 1, resting and maximum HR assessed by both the Polar H10 monitor and the test biosensor will be compared using either *t*-test or Wilcoxon test, based on data distribution. The same comparison will be applied to the step count measured by the test biosensor and the ActiGraph triaxial accelerometer. Intraclass correlation coefficient (ICC) will also be computed, along with Bland–Altman analysis to assess HR and step count agreement.

During phase 2, a quantitative analysis will be conducted on the frequency of possible gamified application failures. Pre- and post-exercise protocol data, including functional capacity, VO_2_, tissue oxygenation, maximum and resting HR, systemic blood pressure, and perceived exertion, will be compared using *t*-test or Wilcoxon test, based on data distribution. Similarly, the number of steps evaluated by the biosensor under test and the ActiGraph accelerometer will undergo the same analysis, along with ICC calculation.

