For phase 3, a qualitative analysis will be performed on participants’ diary reports and a quantitative assessment of potential gamified application failures. Step count measured by the biosensor will be compared to the ActiGraph accelerometer using Student’s *t*-test or Wilcoxon rank-sum test, depending on residual distribution. Agreement between step counts will be evaluated using Bland–Altman test, Lin’s correlation coefficient, and intraclass correlation coefficient. Pre- and post-exercise protocol data, encompassing functional capacity, VO_2_, tissue oxygenation, maximum and resting HR, systemic blood pressure, subjective exertion perception, endothelial function, and HRV, will be analysed using Student’s *t*-test for paired samples or Wilcoxon signed-rank test, aligned with residual distribution. Participants achieving a minimum of 70% completion of the prescribed protocol will be classified as adherent. As the random allocation is anticipated to ensure baseline comparability between the control and intervention groups, unadjusted analyses will primarily be carried out. In the event of any non-comparability in baseline characteristics due to chance, appropriate adjustments will be made to prevent potential biases. Significance level will be set at *p* < 0.05. The data will be analysed using Statistical Package for the Social Sciences (SPSS) 20.0 (SPSS, Chicago, IL, USA).

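### Phase 2 compares biosensor and ActiGraph step counts with a difference test plus an ICC in about 15 people and omits the Bland–Altman analysis planned for phases 1 and 3, so a biased or noisy sensor could appear concordant.

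*Protocol article*

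**What the plan says.** Outcomes {12} lists as the first primary outcome "the concordance between HR and step count measurements assessed by the biosensor under test compared to standard devices". Sample size {14} covers phases 1 and 2 together: "a convenience sample of 15 individuals without medical contraindications for PA will be studied", and "Assuming a sample loss of 30%, we will recruit 20 participants".

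Statistical methods {20a} treats the same step-count question differently in each phase:

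- **Phase 1:** a t-test or Wilcoxon test and an ICC, "along with Bland–Altman analysis to assess HR and step count agreement".
- **Phase 2:** pre- and post-training data "will be compared using *t*-test or Wilcoxon test, based on data distribution". For step counts, "the number of steps evaluated by the biosensor under test and the ActiGraph accelerometer will undergo the same analysis, along with ICC calculation". Bland–Altman is not listed.
- **Phase 3:** a difference test, and in addition "Agreement between step counts will be evaluated using Bland–Altman test, Lin’s correlation coefficient, and intraclass correlation coefficient".

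The only cut-off attached to the tests is "Significance level will be set at *p* < 0.05", stated once at the end of the phase 3 paragraph. The progression criteria later in the same section contain a 5% criterion, expressed as a standard error and assigned to phase 1. Phase 2 progression depends on whether the application works, and data recording failures in earlier phases also count.

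**The concern.** Whether two devices agree and whether a measurement changed after training are different questions, and phase 2 gives them the same test. A difference test takes equality as its null hypothesis, so the result that favours the sensor is failure to reject. In a small sample that is likely even when a relevant bias exists, and it becomes more likely as the sensor gets noisier. Conversely, a very precise sensor can be flagged for a trivial bias. The test also says nothing about scatter in individual people, which is what limits of agreement describe.

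At stake is what phase 2 can report on a primary outcome. Phase 2 moves from the shuttle walk of phase 1 to exercise on a step, under supervision, before unsupervised use in phase 3. Good agreement in walking does not establish agreement in stepping. If phase 2 reports only a p-value and an ICC, a biased or noisy step count could pass without its size being seen.

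**Working it through.** **Inputs from the article.** n = 15 analysed; 20 recruited with 30% loss; significance level 0.05 (sidedness not stated, two-sided assumed).

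**Inputs assumed, because the article gives none.** SD of the paired differences 5% to 20% of mean steps; between-person SD 20% or 30%; ICC cut-offs of 0.75 and 0.90 for illustration only; one paired difference per person.

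**The plan's own figure.** 15 × 1.30 = 19.5, rounded up to 20, which matches. With 20 recruited and 30% lost, 20 × 0.70 = 14 remain, so the analysed number is about 14 or 15. The 15 is a convenience sample, so there is no power statement to reproduce.

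**Miss rate of the paired t-test.** With d = bias / SD of the differences, the statistic follows a noncentral t distribution with n − 1 degrees of freedom and noncentrality d√n. For d = 0.5 and n = 15 the noncentrality is 0.5 × √15 = 1.94 and the critical value is 2.145. Power is 44%, so the miss rate is 56%. At n = 14 it is 59% and at n = 20 it is 44%. Power of 80% at n = 15 needs a bias of 0.78 SD.

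Miss rates at n = 15:

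| True bias | SD 5% | SD 10% | SD 15% | SD 20% |
|---|---|---|---|---|
| 5% | 5% | 56% | 78% | 85% |
| 10% | about 0% | 5% | 33% | 56% |

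With no bias the test is non-significant 95% of the time, whatever the scatter.

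**How far the ICC offsets this.** Let B be the between-person SD, S the SD of the differences and b the bias.

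- Consistency ICC ≈ B² / (B² + S²/2). Bias does not enter.
- Absolute-agreement ICC ≈ B² / (B² + S²/2 + b²/2).

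For B = 20, S = 10, b = 5: consistency 400 / 450 = 0.89; absolute agreement 400 / 462.5 = 0.86.

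A simulation of 20,000 trials at n = 15 gives the chance of a non-significant t-test together with an absolute-agreement ICC at or above the cut-off:

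| Between-person SD | Bias, SD of differences | Expected ICC | Non-significant and ICC ≥ 0.75 | Non-significant and ICC ≥ 0.90 |
|---|---|---|---|---|
| 20% | 5%, 10% | 0.86 | 51% | 17% |
| 20% | 10%, 15% | 0.71 | 15% | 0.6% |
| 20% | 0%, 20% | 0.67 | 23% | 0.3% |
| 30% | 5%, 10% | 0.94 | 56% | 47% |
| 30% | 10%, 15% | 0.85 | 29% | 8% |
| 30% | 0%, 20% | 0.82 | 72% | 10% |

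A 10% bias with SD 5% is detected almost always. The protection from the ICC therefore runs from nearly complete to slight, depending on inputs that are not given.

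**What Bland–Altman would show.** The limits are bias ± 1.96 SD. For bias 5% and SD 10%: 5 ± 19.6, or −14.6% to +24.6%. For no bias and SD 20%: −39.2% to +39.2%. At n = 15 the 95% confidence interval of each limit is about ± 2.145 × √(3/15) = ± 0.96 SD. The limits are imprecise, but bias and scatter are both visible.

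**The case against.** The strongest reply is that phase 2 is not where the sensor is validated. Trial design {8} and the phase 1 description assign biosensor validation to phase 1, which is run in a laboratory by trained researchers. Phase 1 has ICC, Bland–Altman and a 5% progression criterion, and phase 3 has Bland–Altman, Lin's coefficient and ICC. Phase 2 progression rests on the application, so no stated decision depends on the step-count test. This stands, and it limits the consequence. It does not explain why a comparison the plan chose to make, on a primary outcome, uses a weaker method than the phases on either side.

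Two stronger readings are tempting, and the documents support neither:

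- **A poor sensor would be declared concordant.** No sentence says that a non-significant test, or any ICC value, will be taken as agreement. The ICC falls with scatter and, in its absolute-agreement form, with bias.
- **Phase 2 fails because it lacks a numerical tolerance or ICC cut-off.** Such detail is commonly left to an analysis plan, which is not shown here. The phase 1 figure of 5% is a standard-error criterion, not a limit on mean step bias, and cannot simply be carried over.

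It is also fair to say that the article does not state which phase 2 recordings are compared: the repeated walk tests, the training sessions, or an average over sessions. Averaging would shrink the within-person part of the scatter and could lower the miss rates above.

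**Conclusion.** The point holds as an inconsistent and unsuitable choice of method in one phase. The phase 2 step-count comparison is fixed as a difference test plus an ICC in about 15 people, without the agreement analysis planned for the same primary outcome in phases 1 and 3. A non-significant result there does not show agreement: a bias of 0.5 SD of the differences is missed 56% of the time at n = 15. That figure assumes a two-sided paired t-test and one difference per person. Translating it into percentage step bias, or into a joint result with the ICC, needs the SD of the differences, the between-person spread and the ICC form, none of which is given, so those results are a range and not an estimate. The supportable conclusion is that a biased or noisy sensor could appear concordant in phase 2. The omission affects what phase 2 can report on concordance, not a stated progression decision.

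**What to change.** In the phase 2 paragraph of Statistical methods {20a}:

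- Make Bland–Altman the agreement analysis for step counts, as in phases 1 and 3: mean paired difference (biosensor minus ActiGraph) with its confidence interval, and 95% limits of agreement.
- Report the ICC in its absolute-agreement form, with a confidence interval.
- Keep the t-test or Wilcoxon test as descriptive only, and state that non-significance is not evidence of agreement.

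No new ±5% pass/fail rule is needed. If a 90% interval had to lie within ±5%, a sensor with no bias would pass about 96%, 49% and 20% of the time at assumed SDs of 5%, 8% and 10% with n = 15, which is too demanding for a convenience sample of this size.

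The cost is a wording change and slightly more analysis, with no new data or participants. Limits at n = 15 will be wide, so the conclusion may be less favourable to the sensor.

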### Phase 3: Evaluation of gamified in uncontrolled environment

Phase 3 comprises a noninferiority, investigator-blinded, randomized clinical trial with two distinct groups: the intervention and control groups. Participants within the intervention group (IG) will install the gamified application on their smartphones and use a biosensor during exercise sessions. These sessions will align with the prescribed intensity derived from the ISWT, following the 6-week regimen detailed in phase 2. Participants will be duly instructed to cease exercising if they experience symptoms like chest pain, discomfort, or dizziness.

Within the gamified application, participants will have access to a diary feature, enabling them to log notifications received and their efforts during exercise, both monitored by the biosensor and the gamified app. On the other hand, individuals in the control group (CG) will receive instructions to engage in physical activity at home without biosensor monitoring. They will use the app independently, aiming for a minimum of 300 min per week at moderate intensity or at least 150 min per week at vigorous intensity (self-assessed).

Preceding and following the 6-week period, both the IG and CG will undergo assessments akin to those conducted in phase 1. These include evaluations of functional capacity, muscle oxygenation, and further assessments led by trained and blinded researchers.

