### Methods in analysis to handle protocol non-adherence and any statistical methods to handle missing data {20c}

Intention-to-treat (ITT) analyses will be carried out for the primary outcomes to uphold the initial randomization and maintain the real-world context of participants’ treatment assignments. This approach involves including all randomized participants within their originally allocated groups, ensuring the preservation of the study’s initial design.

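### The only test named for phase 3 ISWT, VO2 and the secondary outcomes is a paired pre-post test; no between-arm test or effect estimate is named for them

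*Protocol article*

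**What the plan says.** The section on phase 3 of the protocol article describes a "randomized clinical trial with two distinct groups: the intervention and control groups". Both arms are assessed before and after the six weeks. Outcomes {12} lists as a primary outcome the "evaluation of exercise capacity through ISWT, including stage and the corresponding phase at which the test was halted", and lists oxygen consumption as another. Tissue oxygenation, perceived exertion, endothelial function and autonomic function are secondary.

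For phase 3, Statistical methods {20a} groups functional capacity, VO2, tissue oxygenation and heart rate with "systemic blood pressure, subjective exertion perception, endothelial function, and HRV, will be analysed using" a Student's t-test "for paired samples or Wilcoxon signed-rank test, aligned with residual distribution". The only other phase 3 significance test it names concerns devices: "Step count measured by the biosensor will be compared to the ActiGraph accelerometer using" a t-test or rank-sum test. It then says that, because randomisation should make the groups comparable at baseline, "unadjusted analyses will primarily be carried out", with adjustment if chance imbalance appears.

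Section {20c} promises intention-to-treat analysis for the primary outcomes: "This approach involves including all randomized participants within their originally allocated groups".

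**The concern.** A paired t-test or signed-rank test asks whether people changed between two visits. It does not ask whether the intervention group (IG) changed more than the control group (CG), which is the question randomisation is there to answer. It also cannot supply the IG−CG difference and confidence interval that any noninferiority reading would need. Phase 2, which has no control group, uses essentially the same pre-post tests, and there they fit the design.

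The control group is also told to exercise, with weekly targets of 300 minutes at moderate or 150 minutes at vigorous intensity. Improvement in both arms is therefore plausible, and a significant pre-post change in IG would say little about the intervention itself. With no between-arm test named, the results invite a reading of the form: IG changed significantly, CG did not, so the intervention works. That is not a test of the difference.

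The allocation section gives variability of VO2 with age and gender as the reason for block randomisation. The design thus aims to balance the arms for VO2, while the test named for VO2 does not compare them.

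**Working it through.** **1. What each named phase 3 test compares** (Statistical methods {20a})
- Paired t-test or signed-rank test: post against pre in the same person; no arm contrast.
- t-test or rank-sum test on step count: biosensor against ActiGraph; no arm contrast.
- Bland–Altman, Lin and intraclass coefficients: device agreement; no arm contrast.
- Unadjusted analyses, adjusted if imbalance occurs: an arm comparison is implied, but no test, contrast or effect measure is given.

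**2. The plan's own figure** (Sample size {14}). Inputs: adherence 70% and 50%, 95% confidence, 80% power, 1:1.
- Two-sided two-proportion formula: n = [1.96·√(2·0.6·0.4) + 0.8416·√(0.7·0.3 + 0.5·0.5)]² / 0.2² = (1.358 + 0.571)² / 0.04 ≈ 93.
- With continuity correction: (93/4)·[1 + √(1 + 4/(93·0.2))]² ≈ 103, against the stated 104.
- Loss of 30%: 104/0.70 = 148.6, so 149 per arm and 298 in all, as stated.

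The size is reproduced to within one person per arm. It is built on a between-arm contrast of adherence. The paired tests contain no such contrast.

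**3. What would follow if the arms were judged by their separate paired tests.** Assume the same true change in both arms, and per-arm power p. The arms are independent, so P(exactly one significant) = 2p(1−p), and half of these cases favour IG. At p = 0.05 (no change) this is 2·0.05·0.95 = 9.5%. At p = 0.5 it is 50%, the maximum. At p = 0.8 it is 32%.

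A simulation with 104 completers per arm and two-sided 0.05 (20,000 trials; 2,000 for the pooled test) gave the figures below. The documents give no SD or expected change for ISWT or VO2, so the first column is an assumption.

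| True change, each arm (SD of change) | p | 2p(1−p) | Simulated: exactly one arm significant | Between-arm t-test on change | Paired test pooling both arms |
|---|---|---|---|---|---|
| 0 | 0.050 | 9.4% | 9.4% | 4.8% | 5.2% |
| 0.1 | 0.172 | 28.4% | 28.5% | 4.8% | 30.3% |
| 0.2 | 0.532 | 49.8% | 49.6% | 4.9% | 82.6% |
| 0.3 | 0.859 | 24.2% | 24.2% | 4.9% | 99.1% |
| 0.5 | 0.999 | 0.3% | 0.2% | 4.8% | 100% |

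The between-arm test keeps its 5% level throughout. The protocol does not say whether the paired test is run per arm or on everyone together. Pooling does not help: it detects common change, not an arm effect.

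**4. Missing 6-week values.** At the anticipated 30% loss, 149·0.30 = 44.7, about 45 per arm (298·0.30 ≈ 89 in all), would be absent from any complete-case analysis.

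**The case against.** Four points can fairly be made on the other side.

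- **An arm comparison is implied.** Talk of unadjusted analyses and of adjusting for chance imbalance makes sense only if the arms are compared. Adherence is explicitly a between-group outcome, and the trial is sized on it. A reader might infer that the randomisation goes unused or that an arm comparison is ruled out; the text does not support that. What stands is narrower: the test actually assigned to these outcomes is a within-person one. A condensed article may leave the detail of a model to an analysis plan, but this article states a test, and the test does not fit the question.

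- **Intention to treat.** A reader might infer that the paired tests break the promise for every outcome by dropping those without a post-test. Section {20c} limits the promise to primary outcomes, so the secondary ones raise no conflict. Nor is the loss peculiar to paired tests: complete-case ANCOVA would lose the same people, and a paired test can be run on imputed data. The article does not say that the analysis will be complete-case.

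- **The 50% figure.** It is the peak of 2p(1−p), and it applies only if someone infers an effect from one arm being significant and the other not. The protocol states no such rule. The whole range has to be shown, and it falls to almost nothing for large changes.

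- **Learning and regression to the mean.** Phase 1 runs two ISWTs and keeps the better, and the phase 3 assessments are similar, which may reduce learning. Participants are selected on a physical activity questionnaire and not on ISWT or VO2, which weakens any argument from regression to the mean. The point does not need either: both arms being told to exercise is enough.

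**Conclusion.** The point holds in a limited form. For phase 3 ISWT capacity, VO2 and the secondary outcomes, the only named test has no arm contrast, and the implied arm comparison has no test or effect estimate attached. Two of these outcomes are primary, so the plan should be corrected before analysis. This conclusion rests on the text alone and on no numerical assumption.

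The size of the possible error is conditional. If arms were judged by separate paired tests and both truly changed equally, a false difference would appear in about 9–10% of trials with no change, in up to 50% at intermediate change, and in almost none at 0.5 SD. This is the risk of an inference the wording leaves open. It is not an error rate of a decision rule in the protocol. The intention-to-treat issue is secondary and concerns ISWT and VO2 only.

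**What to change.** In the phase 3 part of Statistical methods {20a}, replace the paired tests with a between-arm analysis:

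- ANCOVA of the 6-week value on arm and the baseline value of the same outcome, plus age and sex, which the randomisation is meant to balance. Report the IG−CG difference with its 95% CI.
- A rank-based between-arm alternative where the distribution requires it. ISWT stage is discrete, so this may matter.
- Within-arm changes kept as description.
- For ISWT and VO2, handle missing 6-week values in a way consistent with section {20c}, for example by multiple imputation.

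One caution applies. Participant timeline {13} places the initial assessment after randomisation, and participants are not blinded, so an effort-dependent baseline could be affected by knowledge of allocation. Take the baseline before allocation is disclosed, or check its balance before adjusting. For the same reason, a model that forces equal baseline means would be doubtful here.

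The cost is protocol and analysis plan wording, slightly more analysis work and a model assumption. Baseline values are already planned, and age and sex are already needed for the intended balance. The change supplies the estimate that a noninferiority reading needs; it does not set a margin.
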